#### Exploratory outcomes

|                                              |                                                                                                                                                                                                                                                           |                                                                                                                          |
|----------------------------------------------|-----------------------------------------------------------------------------------------------------------------------------------------------------------------------------------------------------------------------------------------------------------|--------------------------------------------------------------------------------------------------------------------------|
| Stroke recurrence                            | Participants self-reported whether they had experienced stroke events during the 12-months follow-up period.                                                                                                                                              | Binary as experienced a stroke event vs. not experienced a stroke event                                                  |
| Degree of Disability (Modified Rankin Scale) | Participants' degree of disability evaluated based on assessors' observation and participants' self-reported symptoms or disability. A score ranged from 0 (no symptoms) to 5 (severe disability). A score of $\leq 2$ indicates functional independence. | Binary as score 0-1 (no symptoms at all or no significant disability despite symptom) vs (moderate to severe disability) |
| Stroke-related hospitalization               | Participants self-reported whether they were admitted in the hospital due to stroke event.                                                                                                                                                                | Binary as hospitalized due to stroke vs. not hospitalized due to stroke                                                  |
| Mortality                                    | Report on whether the participant died during the 12-months follow-up period                                                                                                                                                                              | Binary as diseased vs alive                                                                                              |

1009

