5. Randomization: The randomization was performed by an independent statistician from Duke University with blinding to the identity of the cluster and village doctors. The 50 villages were randomized in a 1:1 allocation ratio to the intervention or control arm with stratification by the five townships. The results of the randomization were blinded among all research staffs who participate in the recruitment and baseline assessment. The allocation of the randomization in a township were informed by a message from the Principle Investigator to the village doctor and local project manager once participants in a township were all recruited and completed the baseline assessment.
- 7a. Intervention delivery: Village doctors and stroke survivors received the SINEMA intervention. No blinding for village doctors and patients was possible.
- 7b. Patients received usual care. No blinding for village doctors and patients was possible.
8. Participant outcome assessment at 12 months: Data were collected by independent blinded trained research staff (same group of people with the baseline assessment). Face-to-face interview and standard anthropometric measurements were performed.

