Data on hospitalization and recurrence of stroke will be collected through extracting the data from county medical insurance system and death record system. Data on hospitalization will be extracted every month from the medical insurance system, which includes the reason and duration of the hospitalization. Death data will be extracted through the death report from the local CDC and verified through a smartphone-based shortened version of verbal autopsy survey administered by county project officer to family members of dead participants in this study. The survey has been proved to be feasible and acceptable in rural north China. Respecting the culturally appropriate grieving period, the interview will be conducted at the sixth and twelfth month after initial of the intervention. **Table 2** shows the overall data collection procedures based on SPIRIT guideline.

803 Table 2. The schedule of enrollment, intervention and assessments

|                                                         | STUDY PERIOD |                     |                              |                                                                                       |       |       |      |       |                      |
|---------------------------------------------------------|--------------|---------------------|------------------------------|---------------------------------------------------------------------------------------|-------|-------|------|-------|----------------------|
|                                                         | Enrollment   | Baseline Assessment | Allocation of treatment arms | Post-allocation                                                                       |       |       |      |       | Close-out Assessment |
| \TIMEPOINT                                              | -3 mon       | -2 mon              | 0 mon                        | 0 mon                                                                                 | 3 mon | 6 mon | 9mon | 12mon | 13 mon               |
| ENROLMENT:                                       |              |                     |                              |                                                                                       |       |       |      |       |                      |

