Exploratory outcomes include stroke recurrence, hospitalization, disability and mortality, which will be collected through questionnaire or medical insurance records. (See **Table 3**) In addition, based on the mortality data we collect, we will conduct a smartphone-based shortened version of verbal autopsy (VA) survey to family members of dead participants in this study, to improve the quality of cause of death data. This survey has been proved to be feasible and acceptable in rural north China by our study team 1. We will use the Population Health Metrics Consortium (PHMRC) Shortened Questionnaire adult module (see **Appendix A-5**, bilingual and adjusted for SINEMA study), which has been validated and elicits sufficient information to diagnose most probable cause of death of public health importance. Trained health workers will conduct the VA interview, which will take about 30 minutes. Respecting the culturally appropriate grieving period, the VA interview will be conducted within 4-12 months after the date of death. An appropriate respondent (usually the family member) must be identified, and informed consent (see **Appendix A-1**) must be obtained before the interview. The trained VA interviewer will conduct the interviews in the local language.

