**Table 3. Outcome variables in baseline and follow-up survey**

| Outcomes                          | Measures                 | Methods                                |
|-----------------------------------|--------------------------|----------------------------------------|
| Outcomes for participants: |                          |                                        |
| Primary outcome:                  | Systolic Blood Pressure  | Electronic BP monitor*                 |
| Secondary outcome:                | Diastolic Blood Pressure | Electronic BP monitor*                 |
|                                   | Mobility                 | Timed Up and Go test 55,56* |

|                                         |                                                     |                                                                |
|-----------------------------------------|-----------------------------------------------------|----------------------------------------------------------------|
| Exploratory
outcomes:                | Medication adherence                                | Questionnaire: MMAS-4 57*                           |
|                                         | Physical activity level                             | Questionnaire: IPAQ short form 58*                  |
|                                         | Quality of life                                     | Questionnaire: EQ5D 54*                             |
|                                         | Stroke recurrence                                   | Questionnaire and medical insurance records**                  |
| Outcome for
village doctors: | Stroke related morbidity                            | Questionnaire and medical insurance records**                  |
|                                         | Stroke related mortality                            | Questionnaire, death records and verbal autopsy *** |
|                                         | Knowledge, attitude and practice of village doctors | Questionnaire self-administered by village doctors             |

\* The outcomes for participants will be measured by trained staff recruited from Center of Disease Prevention and Control of a nearby county, who are complete blinded of randomized allocation of villages and will not be involved in the implementation of the intervention.

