## DISABILITY AND DEPENDENCE

### Modified Rankin Scale

- ☐ No symptoms at all
- ☐ No significant disability despite symptoms; able to carry out all usual duties and activities
- ☐ Slight disability; unable to carry out all previous activities, but able to look after own affairs without assistance
- ☐ Moderate disability; requiring some help, but able to walk without assistance
- ☐ Moderately severe disability; unable to walk without assistance and unable to attend to own bodily needs without assistance
- ☐ Severe disability; bedridden, incontinent and requiring constant nursing care and attention

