### 3.4.3 Subgroup analyses

The subgroup analysis will be conducted by following the published statistical analysis plan to include subgroup analysis on gender (male/female), age group (<65 vs. ≥65), education level (schooling vs. no schooling), type of stroke (hemorrhage vs. ischemic stroke), years since last stroke events (less than 3 years vs. more than 3 years), and having benefit package for Chronic Diseases Outpatients (have benefit package vs. does not have the benefit package), Patient Health Questionnaire (PHQ-2) score (0-2 vs. 3-6). We will also conduct additional subgroups by marital status (married vs. widowed, divorced, or not married), annual household income (<5,000 vs. ≥5,000), years since the first stroke events (less than 5 years vs. more than 5 years), disability status (moderate to severe disability vs. no to slight disability). These subgroup analyses will be performed by adding to the model both the variable and its interaction term with treatment arm. We caution that these analyses may be not powered.

For mortality analysis, subgroup analyses will be conducted following the subgroups prespecified for the one-year outcome analysis. Additional subgroup analyses by considering

the baseline status of annual income (<5,000 vs. ≥5,000), marital status (married vs. widowed, divorced, or not married), systolic blood pressure (≥ 140 mm Hg vs. < 140 mm Hg), and disability status (moderate to severe disability vs. non-disability to slight disability) will also be conducted. Subgroup variable and its interaction term with the intervention were added to the minimally adjusted model used in the primary analysis as fixed effects in the subgroup analysis.

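### Table 4 defines stroke recurrence and stroke hospitalisation by self-report alone, against the record sources named elsewhere, so fatal recurrences have no value; the mRS split leaves score 2 and deaths unassigned.

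*Combined protocol and SAP*

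**What the plan says.** **Recurrence and hospitalisation.** Under Exploratory outcomes, Table 4 defines recurrence as "Participants self-reported whether they had experienced stroke events during the 12-months follow-up period", and defines stroke-related hospitalisation as self-reported admission for a stroke event. Three other places in Part A give different sources:

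- Section 5.6: "Data on hospitalization and recurrence of stroke will be collected through extracting the data from county medical insurance system and death record system". Hospitalisation is to be extracted monthly, with reason and duration.
- Section 5.7: the exploratory outcomes "will be collected through questionnaire or medical insurance records".
- Table 3, recurrence row: "Questionnaire and medical insurance records".

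The exploratory analysis section (modified Poisson GEE) does not rank these sources.

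**Disability.** Table 4 scores the mRS from 0 to 5 and specifies "Binary as score 0-1 (no symptoms at all or no significant disability despite symptom) vs (moderate to severe disability". Only the better category has a score range. The third level of the scale in Appendix A-3, score 2, reads "Slight disability; unable to carry out all previous activities, but able to look after own affairs without assistance". The same Table 4 row treats scores up to 2 as functional independence. Part B section 3.4.3 forms a baseline subgroup by "disability status (moderate to severe disability vs. no to slight disability".

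**Deaths.** Section 7.1.1 takes as its population everyone enrolled with a baseline assessment, and says that follow-up missing because of death will be allowed for, without saying how. Section 7.5 plans no imputation in the primary analysis. It allows adjustment for baseline predictors of loss and possibly a pattern mixture analysis. Mortality is a separate exploratory outcome.

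**The concern.** A participant killed by a recurrent stroke cannot report it. Under the Table 4 wording that person has no recurrence value, and the value is missing because the event happened. Treating this as missing at random, or adjusting for baseline covariates, does not restore an event that the death record already shows. The comparison then covers attending survivors and not the population promised in section 7.1.1. If the arms differ in how often a recurrence is fatal, the risk ratio is biased.

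Self-report also comes from people who know their allocation: the Figure 7 notes say "No blinding for village doctors and patients was possible". Insurance records do not depend on recall.

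For the mRS, an analyst could place score 2 with the better group, place it with the worse group or leave it out, and could make that choice after seeing the data. Deaths have no level on a 0 to 5 scale.

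The matter carries into Part B. Section 3.3.2 makes recurrence, stroke hospitalisation and disability secondary outcomes, the first two again by self-report, over a longer period in which more participants will have died.

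**Working it through.** **Plan's own figure.** The documents give no power or event count for these outcomes. The stated 83% power is for systolic pressure, and it reproduces. The design effect is 1 + (24 − 1) × 0.04 = 1.92. With 23 × 24 = 552 per arm, the effective size is 552/1.92 = 287.5. A noncentral t calculation for 5 mmHg with SD 20 gives 83.4% on 44 df. Nothing below changes it.

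**Sources side by side (Part A).**

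| Outcome | Table 4 | Section 5.6 | Section 5.7 | Table 3 |
|---|---|---|---|---|
| Recurrence | self-report | insurance and death records | questionnaire or insurance | questionnaire and insurance |
| Stroke hospitalisation | self-report | insurance and death records; hospitalisation monthly from insurance | questionnaire or insurance | no row of that name |
| Fatal stroke | no recurrence value | death record | not addressed as recurrence | under stroke-related mortality only |

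**Illustration for recurrence.** Inputs: 625 per arm (1,250/2, section 5.3) and 11.2% first-year recurrence (Background), so 625 × 0.112 = 70 events per arm. The 11.2% is a literature figure for stroke survivors, not a projection for this sample of prevalent cases. Case fatality f is assumed at 10%, 20% or 30%. Non-stroke deaths and other losses are ignored.

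Survivor-only risk = (70 − 70f)/(625 − 70f):

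- f = 10%: 63/618 = 10.2%
- f = 20%: 56/611 = 9.2%
- f = 30%: 49/604 = 8.1%

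With equal true recurrence (true ratio 1.00), the intervention-to-control ratio becomes:

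- control 30%, intervention 10%: (63/618)/(49/604) = 1.26
- control 10%, intervention 20%: (56/611)/(63/618) = 0.90
- control 10%, intervention 30%: (49/604)/(63/618) = 0.80

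If the intervention prevented every fatal stroke and nothing else:

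- f = 10%: true ratio 63/70 = 0.90; seen as (63/625)/(63/618) = 0.99
- f = 20%: true ratio 56/70 = 0.80; seen as (56/625)/(56/611) = 0.98
- f = 30%: true ratio 49/70 = 0.70; seen as (49/625)/(49/604) = 0.97

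So the survivor-only ratio can move up, down or towards 1.

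**Illustration for the mRS.** Part B section 3.1 reports 1,266 survivors assessed at 12 months. If 10% to 30% had score 2 (assumed), that is 127 to 380 people. With an assumed 50/25/25 split across 0–1, 2 and 3–5, the better-outcome share is 50% if score 2 joins 3–5, 75% if it joins 0–1, and 50/75 = 67% if it is dropped.

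**The case against.** The best reply is that this is a drafting mismatch. Section 5.6 already names the death record system, sections 5.6 and 5.7 and Table 3 name insurance records, and stroke-related mortality is collected through death records and verbal autopsy. A reader might infer that fatal strokes are never counted anywhere in the plan. The documents do not support that: it is true of the Table 4 wording only. What stands is that Table 4 is where the analysed variable is defined, and counting deaths separately does not mend the recurrence comparison.

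Self-report is also firmer than it sounds. Appendix A-3 limits recurrence to episodes needing a visit or admission at county level or above, and the assessors are blinded. This helps with accuracy among survivors and does nothing for the dead.

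A reader might infer that an intervention that makes strokes less deadly is bound to look worse. The calculation does not support a direction, and no case fatality is given. Even the 1.26 scenario is modest against sampling error. The standard error of the log ratio is √(1/63 − 1/618 + 1/49 − 1/604) = 0.18, a 95% interval of about 0.88 to 1.79 before clustering.

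On the mRS, score 2 is a middle level, and the likeliest explanation is that a range of 2–5 was left off the second category. It would be wrong to conclude that hundreds of participants will be discarded. The Part B grouping is a baseline subgroup and does not by itself contradict an outcome cut. The gap is still open on the page.

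**Conclusion.** The point holds as a conflict between Table 4 and the data-collection sections, with a specific consequence. Under Table 4 as written, fatal recurrences have no value and the comparison is confined to attending survivors. Sections 7.1.1 and 7.5 do not repair this. With assumed case fatalities of 10% to 30% and the background recurrence rate, a true ratio of 1.00 could appear anywhere from 0.80 to 1.26, and a benefit confined to fatal strokes would nearly vanish. These sizes are illustrative, and the direction is unknown.

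The mRS definition is incomplete: score 2 is unassigned by label, the 0–1 cut sits beside a different threshold in the same row, and deaths have no rule. The documents do not show that any particular cut is right.

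The reach is limited. The outcomes are exploratory in Part A and secondary in Part B, and the primary systolic pressure analysis and its power are untouched.

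**What to change.** **Part A, Table 4.**

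- Recurrence, for all enrolled participants: a stroke admission in the insurance record, or a stroke death (death record or verbal autopsy), or self-report. Add a records-only sensitivity analysis, because self-report is unblinded. Say whether a death coded to stroke without a recorded acute event counts.
- Stroke hospitalisation: the insurance record, with self-report as a sensitivity analysis.
- mRS: print both categories as score ranges so that score 2 is assigned, and reconcile the 0–1 cut with the functional-independence threshold of 2 in the same row. State how deaths enter, for example by a sensitivity analysis that counts death in the worse category. The choice of cut is the sponsor's.
- Bring sections 5.6, 5.7 and Table 3 into line with these definitions.

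**Part B.** Count stroke deaths from the sources already planned in section 3.2.2 (death registry, village doctor reports and verbal autopsy) as recurrences. Do not assume insurance data, since section 3.2.2 plans death-registry linkage and section 3.3.2 self-report. State the time window, because the Part B questionnaire asks survivors about recurrence in the past year.

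**Cost.** Revised wording and, for Part A, one data merge. The insurance and death records are already to be extracted, and section 6.3 keeps identifiers for matching with the health information system. The merge must be done before identifiers are removed from the analysis file. Insurance coding may miss mild untreated strokes, which self-report still picks up in the main definition.

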### 5.3 Sample size

Based on a sample of 1,250 prevalent stroke patients in 50 villages (with 25 villages per arm and on average 25 patients per village), assuming loss of 2 clusters (villages) per arm and loss of 1 patient per village on average, an intra-cluster correlation coefficient (ICC) of 0.04 (a conservative assumption), and a standard deviation (SD) for SBP pre-post change of 20 mmHg, the study has 83% power (with 2-sided alpha = 0.05) to detect a 5 mmHg net difference in pre-post change of SBP between intervention and usual care arms. Previous studies have been demonstrated that a 5mmHg difference is a meaningful change for stroke recurrence in 3-5 years. The effect size of a 5mmHg difference corresponds to a standardized effect size of 0.25 (5/20) and therefore we will have more than 80% power to detect such standardized effect sizes for secondary outcomes of interest, assuming the same level of clustering of those outcomes.

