### 7.3.2 Exploratory effectiveness analyses

The exploratory outcomes of mortality, disability, stroke-related hospitalization, and stroke recurrence are binary variables. The modified Poisson GEE approach (with log-link) will be used to obtain risk ratios for binary outcomes, as described above.

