### 3.3.2 Secondary outcomes

The secondary outcomes of interests will be in line with the original protocol, including diastolic blood pressure, medication adherence (measured by using 4-item Morisky Green Levine Scale), physical activity level (measured by using IPAQ-short form), mobility (measured by using Timed-up and go test), health-related quality of life (measured by using EQ-5D-5L), disability (measured by using modified Rankin Scale), stroke recurrence (measured by self-reported experience of stroke recurrence) and stroke-related hospitalization (measured by self-reported history of hospitalization).

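### Disability (mRS) is analysed only as a binary outcome, and the Part A model does not use the baseline mRS that the trial collects

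*Combined protocol and SAP*

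**What the plan says.** Appendix A-3, used at baseline and follow-up, records the mRS in six ordered categories, and Table 4 (Section 7.3) scores it 0 to 5. Table B-1 in Part B ticks it at baseline, one year and post-trial.

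Table 4 specifies the analysis variable as "Binary as score 0-1 (no symptoms at all or no significant disability despite symptom) vs (moderate to severe disability". The section on exploratory analyses (the second of the two numbered 7.3.2) states: "The exploratory outcomes of mortality, disability, stroke-related hospitalization, and stroke recurrence are binary variables". It takes its method, modified Poisson GEE, from the preceding section on binary secondary outcomes. That section names the township strata as fixed effects and does not mention baseline value, age or sex.

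Other models in the same documents do use the baseline value:
- The SBP model in Section 7.2 includes baseline SBP, gender and age, and Section 7.3.1 applies the same approach to the continuous secondary outcomes.
- Part B, Section 3.4.1, adjusts binary outcomes for township, age, sex and the baseline outcome.

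Part B, Section 3.3.2, raises "disability (measured by using modified Rankin Scale" to a secondary outcome and keeps the binary method. Neither part contains an ordinal analysis of the mRS.

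**The concern.** Two separate kinds of information are discarded.

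The first is the ordering of the scale. After dichotomising, any movement on one side of the cut counts as no change. An example is a move from level 3 (walks without assistance) to level 4 (cannot walk without assistance).

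The second, in Part A only, is the participant's own baseline mRS. It is already collected, and the rest of the plan treats the baseline value as worth adjusting for.

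Disability matters directly to stroke survivors, and with 50 villages precision is limited. The plan also treats its other functional measures differently. Table 4 analyses both Timed Up and Go and physical activity on the full measure and as a binary variable.

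**Working it through.** **1. Reproduce the plan's own power figure.** The inputs are in Section 5.3. The enrolled design is given as "with 25 villages per arm and on average 25 patients per village". Attrition enters the calculation as "assuming loss of 2 clusters (villages) per arm and loss of 1 patient per village on average". The variance inputs are given as "an intra-cluster correlation coefficient (ICC) of 0.04 (a conservative assumption), and a standard deviation (SD) for SBP pre-post change of 20 mmHg".
- This leaves 23 villages per arm and 24 patients per village, or 552 per arm.
- Design effect = 1 + (24 − 1) × 0.04 = 1.92. Effective n = 552 / 1.92 = 287.5 per arm.
- Noncentrality = 5 / (20 × √(2/287.5)) = 3.00. Noncentral-t power is 83.4% (44 df) or 83.3% (40 df).

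The stated result, "the study has 83% power (with 2-sided alpha = 0.05) to detect a 5 mmHg net difference in pre-post change of SBP", is reproduced. It concerns SBP. The documents give no power, target effect or expected distribution for the mRS.

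**2. Loss from dichotomising alone.** Under proportional odds, the information on the log odds ratio is V = (N/4) × (1 − Σp̄³)/3. Here N = 2 × 287.5 = 575, and p̄ is the mean category probability over the two arms. Power = Φ(ln OR × √V − 1.96). The binary test uses the same formula with two categories (0–1 against 2–5).

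Worked case, with assumed control probabilities for levels 0 to 5 of 0.10, 0.25, 0.30, 0.20, 0.13, 0.02 and OR 1.517:
- Six levels: p̄ = 0.122, 0.278, 0.294, 0.179, 0.110, 0.017. (1 − Σp̄³)/3 = 0.3147, V = 143.75 × 0.3147 = 45.2, and z = 0.4167 × 6.726 = 2.80. Power is 80.0%.
- Two levels: p̄ = 0.40, 0.60. (1 − Σp̄³)/3 = 0.240, V = 34.5, and z = 2.45. Power is 68.7%.
- Loss: 11.3 points.

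Other assumed distributions, each with the OR set so that the shift test has 80% power (OR about 1.51 to 1.60):

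| Controls at mRS 0–1 | Binary power | Loss (points) |
|---|---|---|
| 65% (60% at level 1) | 73.6% | 6.4 |
| 55% (45% at level 1) | 71.9% | 8.1 |
| 55% | 69.5% | 10.5 |
| 35% | 68.7% | 11.3 |
| Even six-way spread | 67.0% | 13.0 |
| 25% | 63.0% | 17.0 |
| 75% | 56.6% | 23.4 |
| 15% | 48.8% | 31.2 |

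A separate latent-normal cluster simulation used a uniform 0.25 SD shift, the same villages and ICC, and five assumed distributions with 20 to 70% of controls at 0–1. It gave 67–72% power for the binary test and 79–82% for ranks, a gap of 8 to 14 points.

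**3. Dependence on effect size.** In the four central rows (55%, 55%, 35%, even) the loss is 3.0 to 5.6 points at OR 1.2 and 1.2 to 1.6 points at OR 2.0. In the most extreme rows it stays larger: 10.6 points at OR 1.2 with 15% at 0–1, and 8.4 at OR 2.0 with 75%.

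**4. Dependence on the shape of the effect.** If the benefit is only 10 percentage points moved from level 2 to level 1, simulation gives 72–89% power for the binary test and 20–27% for the rank test. The ordering of the two analyses then reverses.

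**5. Gain from baseline mRS in the binary model.** These simulations use the same design and a 0.25 SD shift. The assumed individual-level baseline/follow-up correlation is 0.5 to 0.7.
- Baseline varies between villages, but that variation is unrelated to follow-up: about 0 points.
- Baseline has no village-level variation: 2 to 8 points (for example 73.8% to 75.8% at correlation 0.5, and 71.5% to 79.2% at 0.7).
- Village-level correlation also 0.5 to 0.7: about 7 to 18 points.

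**The case against.** Disability is exploratory in Part A. Section 5.3 claims power only for SBP and the secondary outcomes, and Section 7.1.2 ties significance testing to the primary outcome. A pre-specified risk ratio, used alike for every binary outcome, is a legitimate and readable estimand. All of this stands, and it is why the binary result should be kept.

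No mRS-specific input comes from the documents. The 0.25 shift is 5/20 mmHg, borrowed from SBP, and Section 4.3.3 says the final model targets blood pressure, adherence and physical activity. That also stands, so the power figures must be read as conditional.

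A reader might infer that a real shift would probably be missed. The figures do not show that. At the assumed 0.25 shift the binary test has about 67–72% power on the planning numbers (46 × 24 = 1,104 patients). With 25 villages of 25 per arm it has about 72–77%, and Part B, Section 3.1, reports 1,266 participants at 12 months.

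The silence on baseline in Part A may be a drafting gap, since Part B describes its binary analysis as consistent with the one-year plan and yet adjusts for baseline. Section 7.5 would also admit baseline mRS if it predicted loss to follow-up. Neither pre-specifies the adjustment in Part A.

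**Conclusion.** The point holds as a loss of efficiency. The mRS is collected on six levels at every assessment but analysed only as a binary variable, and Part A does not name baseline mRS in the model although it is available and Part B uses it.

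The two losses should be kept apart. Dichotomising costs about 6 to 31 points (8 to 14 in central distributions) when the effect is roughly proportional and a shift test would have about 80% power. In central distributions this falls to about 1 to 6 points at much smaller or larger effects, and the advantage reverses when benefit sits only at the cut. Omitting baseline mRS costs the binary analysis about 0 to 18 points, depending mainly on the village-level baseline/follow-up correlation.

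Two stronger readings are not supported. The sample size statement is not wrong, because it makes no claim about disability in Part A. Nor do the documents show that a shift analysis must replace the risk ratio: that is a choice of estimand on which statisticians can differ.

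**What to change.** 1. In Part A, in the section on exploratory analyses, state that the disability model adjusts for baseline mRS, age and sex as well as township, as Part B does. Say whether baseline enters as the 0–5 score or dichotomised. This is the core change.
2. In Table 4 and in Part B, Section 3.4.1, add a pre-specified proportional-odds analysis of the full mRS. Account for village clustering by a named method (GEE or random intercept), with baseline mRS, township, age and sex as covariates and a stated rule for deaths. Report it beside the binary risk ratio, as Table 4 already does with two forms of Timed Up and Go and physical activity.
3. While editing that row of Table 4, state which side score 2 falls on. The labels do not place it, and the subgroup definition in Part B, Section 3.4.3, groups slight disability with none.

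The cost is SAP wording and one extra model, with no new data. The common odds ratio assumes a roughly proportional shift and is less intuitive than a risk ratio, so the assumption should be checked and both results shown. Part B records that the 12-month assessment took place in July 2018, so anything added to Part A after those data were analysed should be labelled as such.
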